##### Number of Hospital Admissions

This will be quantified at all follow-up time points.

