### 2.2. Design and Setting

A comparative trial will be carried out in the health area of Salamanca (Spain), particularly in the Garrido Sur and Miguel Armijo health centres. Both are urban and have a population with similar characteristics, so they will serve as the intervention and control centre, respectively. The PC nurses at both centres will continue to perform the usual interventions for CPCPs included in the Portfolio of Services of the Castilla y León Health System (SACYL), and case management will be added through a CNCM at the intervention centre.

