### 2.6. Data Collection

Data collection will be carried out by independent evaluators, who will be health professionals from the Salamanca Primary Care Management, with training in the use of the data collection form and the administration of the different tests, which will be paper-based.

The baseline assessment will take place at the patient’s home, and subsequent follow-up assessments will be arranged there or at the health centre depending on their progress:Initial assessment: the variables shown in Table 1 will be collected.Three-, six-, and twelve-month assessment: the same variables as in the initial assessment will be collected, adding the number of readmissions and medicines prescribed, as well as the evaluation of the satisfaction of the user and/or main caregiver.

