### 2.7. Intervention

#### 2.7.1. Common to Both Centres

After planning a hospital discharge, the hospital liaison nurse (HLN) will schedule the CPCP in the agenda of the PC nurse corresponding to the patient in both centres, as usual. All of them will have access to the hospital discharge report via the unified hospital and primary care digital medical record and will contact the patient’s main caregiver to assess their existing needs at home. Moreover, they will continue to perform the usual interventions included in the SACYL Portfolio of Services for CPCP (Figure S1).

Likewise, the evaluators will call the family unit upon discharge from hospital, check the inclusion criteria for this study, explain the research project, and request the signature of the informed consent form if they wish to participate. Subsequently, the initial home assessment will be planned by collecting the data described in Table 1 and the next follow-up assessments at 3, 6, and 12 months will be reported.

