### 2.8. Statistical Analysis

The normality of the variables will be analysed using the Kolmogorov–Smirnov test. Continuous variables will be presented as mean ± standard deviation, or as median and interquartile range in the case of a non-normal distribution. Qualitative variables will be expressed as number and percentage. The association between qualitative variables will be analysed with the chi-square test or Fisher’s test, as appropriate. Comparisons between quantitative variables will be carried out using Student’s *t*-test or the non-parametric Mann–Whitney U test for independent measurements and paired Student’s *t*-test for related measurements. A repeated-measures analysis of variance (ANOVA) will be performed to assess the effect of the intervention between study centres. Covariates will be included in the model to control for potential confounders such as baseline functional status, comorbidities, or characteristics of the main caregiver. An alpha risk of 0.05 will be set as the limit of statistical significance for bilateral hypothesis testing. Data will be analysed with SPSS statistical software version 28.0.

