### 2.9. Strengths and Methodological Limitations of This Study

Although this study follows all the recommendations for non-randomised interventional studies included in the TREND statement, there is a possibility of confounding factors not considered. As this study will be conducted in CPCPs, the loss rate is expected to be high, because their characteristics may prevent them from completing the follow-up due to institutionalisation or death. Given the nature of this study, subjects will not be blinded to the intervention, but the investigator in charge of analysing the data will not be aware of the centre allocation.

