**Data Collection:**					
Sociodemographic variables		√			
Clinical variables		√	√	√	√
Hospital admissions		√	√	√	√
Drugs prescribed		√	√	√	√
Therapeutic adherence			√	√	√
Activities of daily living		√	√	√	√
Quality of life		√	√	√	√
Cognitive performance		√	√	√	√
Caregiver overload		√	√	√	√
Frailty		√	√	√	√
Signs and symptoms of decompensations/exacerbations		√	√	√	√
User satisfaction		√	√	√	√

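### Readmissions are compared between two non-randomised centres with no defined pre-intervention admission count and no specified adjustment for one

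*Protocol article*

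**What the plan says.** One health centre delivers the intervention and the other is the control (Section 2.2: "so they will serve as the intervention and control centre, respectively"). Their comparability is asserted in words: "Both are urban and have a population with similar characteristics". Section 2.9 describes the study as non-randomised and concedes that "there is a possibility of confounding factors not considered".

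Hospital readmissions are a secondary outcome. They are part of the objective (Section 2.1), and a reduction is hypothesised in Section 3. Three places say when they are recorded:

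- Section 2.5.3, Number of Hospital Admissions: "This will be quantified at all follow-up time points".
- Section 2.6 refers the initial assessment to Table 1, then describes the 3-, 6- and 12-month assessments as repeating it, "adding the number of readmissions and medicines prescribed, as well as the evaluation of the satisfaction of the user and/or main caregiver".
- Table 1 has a row "Hospital admissions" ticked at all four assessments, including the initial one. No period is given for the initial entry.

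Section 2.8 assesses the between-centre effect by repeated-measures ANOVA with covariates for "potential confounders such as baseline functional status, comorbidities, or characteristics of the main caregiver". The list is open, and earlier admissions are not among its examples.

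**The concern.** The Barthel Index, COOP-WONCA and MoCA each have a score at the initial assessment, so the analysis can take account of where each centre started. For readmissions the article defines no such value. The Table 1 tick does not supply one as it stands. Every participant enters after a hospitalisation for decompensation (Section 2.3), so an entry recording only that index admission would be the same for everyone and could adjust for nothing.

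Earlier admissions combine severity, social circumstances and local admission habits. If the two centres differ in these, the difference coincides exactly with the treatment comparison. It can look like a case-management effect if the intervention centre is habitually lower, or conceal a real one if the control centre is. Function, comorbidity and caregiver characteristics capture only part of it.

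**Working it through.** **The plan's own figure.** The only calculation in the article is for the Barthel Index (Section 2.4): difference 15, SD 34.8, two-sided alpha 0.05, power 80%, 20% loss. Per group, 2 × (34.8 × (1.960 + 0.842) / 15)² = 84.49; 84.49 / 0.8 = 105.6, rounded up to 106, or 212 in total. This reproduces exactly and is not in dispute. Nothing is sized on readmissions, and no admission rates are given for either centre, so every rate below is an assumption.

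**Simulation 1: rate model.** 106 per centre, 400 runs per setting. Prior-year and follow-up counts are Poisson with a shared gamma-distributed patient rate (mean 1.0-1.5 a year, shape 1-2). The analysis is Poisson regression with robust standard errors, with and without log(prior count + 0.5), and no other covariates.

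- No true effect, intervention centre 25% lower. Unadjusted: rate ratio 0.74-0.75, p < 0.05 in 30%, 37% and 50% of trials across three settings. Adjusted: rate ratio 0.83-0.88, p < 0.05 in 13%, 16% and 28%.
- Equal centres, true rate ratio 0.70. Power 44%, 45% and 61% unadjusted; 56%, 65% and 71% adjusted, a gain of 12, 20 and 10 points.

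A separate run of the same model (600 runs per setting) gave 30-48% falling to 15-25% for false positives, and power rising from 40-62% to 51-70% (11 points at the lower end, 8 at the upper).

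**Simulation 2: simpler tests and other gaps.** Means 1.0-2.0 a year, gamma variance 1, 85 to 106 per centre (85 being roughly 106 after 20% loss), no true effect, 1000 runs per setting. Share of trials with p < 0.05:

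| Intervention centre lower by | Unadjusted t-test | Linear model with prior-year count |
|---|---|---|
| 0% | 5-7% | 4-6% |
| 10% | 7-9% | 5-6% |
| 20% | 17-26% | 7-11% |
| 30% | 35-51% | 12-17% |
| 40% | 60-80% | 21-27% |

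**How much bias is left after adjustment.** In the linear model the share remaining is 1 − b, where b is the pooled within-centre slope of follow-up count on prior count: the sum over centres of var(rate), divided by the sum of var(rate) + mean(rate). For means 1.0 and 0.7 with gamma variance 1, b = (1 + 0.49) / (2 + 1.19) = 0.47, leaving 53%; the simulation at 85 per centre gave 0.162 / 0.304 = 53%. For means 2.0 and 1.4, b = (4 + 1.96) / (6 + 3.36) = 0.64, leaving 36%; the simulation gave 0.220 / 0.605 = 36%. In the rate model, log 0.83 / log 0.75 = 0.65 and log 0.88 / log 0.75 = 0.44. One year of counts measures a patient's habitual rate imperfectly, so roughly a third to two thirds of the gap survives.

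**The opposite direction.** If the control centre is habitually 25% lower and case management truly has a rate ratio of 0.70, the unadjusted ratio is expected near 0.70 / 0.75 = 0.93, and most of a real benefit disappears.

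**The case against.** Two stronger readings are tempting, and the article supports neither.

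A reader might infer that readmissions will be compared with no adjustment. Section 2.8 plans a covariate-adjusted model, its list is given by example, and nothing excludes earlier admissions. The final covariate list for a secondary outcome may also sit in an analysis plan that is not shown. A reader might also infer that a spurious effect will appear. No centre rates are given, Section 2.2 asserts similar populations, the entry criteria narrow the case mix, and a gap could run either way.

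It can further be said that Section 2.6 sends the initial assessment to Table 1, so a baseline entry is scheduled; that the 30-50% figure comes from a model with no covariates, which is not what is planned; and that this is a secondary outcome in a study described as a pilot.

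All of this stands, and it limits the point. It does not remove it. The text and Table 1 disagree on when admissions are first recorded, and a tick without a time window is not a usable covariate. A covariate with no defined window cannot be collected alike at both centres. The named covariates are only partial substitutes for admission history. The precision gain holds even if the centres are identical.

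**Conclusion.** The point holds as one of specification. For an outcome with a stated hypothesis, in a design with one non-randomised centre per arm, the article defines no pre-intervention admission count, names no adjustment for one, and is inconsistent about whether one is collected. A pre-existing centre difference can mimic or hide an effect.

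Under the assumed rates and a 25% gap, with no other covariates, adjustment lowers false-positive findings from about 30-50% to about 13-28%. With equal centres and a true rate ratio of 0.70, it raises power by roughly 8-20 points. These figures are illustrative. The gain over a model already holding function and comorbidities would be smaller, and no calculation here measures that increment. The documents do not show that the centres differ in habitual admissions. The change is worth making, but it affects a secondary outcome and leaves the sample size untouched.

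**What to change.** 1. Reconcile Section 2.5.3 (Number of Hospital Admissions), Section 2.6 and Table 1 on when admissions are recorded.
2. Define the initial Table 1 entry as the number of admissions in the 12 months before the index admission, excluding the index admission itself, taken in the same way at both centres from the "unified hospital and primary care digital medical record" (Section 2.7.1).
3. Report that count by centre with the baseline characteristics.
4. In Section 2.8, name it as a covariate in the readmission model, alongside those already planned.

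The cost is about one record query per patient and one covariate; the count can also be retrieved for patients already enrolled. This presumes that the evaluators can see the admission history. Section 2.7.1 establishes only that the nurses can reach the discharge report through the shared record, so access should be confirmed. The article should also say that adjustment removes only part of a centre gap and that, with one centre per arm, the remaining centre effect cannot be separated from the intervention.

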##### Number of Drugs Chronically Prescribed

This will be recorded from the electronic prescription of the CPCPs at discharge and at the end of follow-up.

##### Therapeutic Adherence

This will be calculated using a scale designed to assess the patient’s skills and knowledge of the prescribed treatment, with items adapted from the DRUGS and Med-Take scales. For each drug, the following criteria are scored with 1 or 0 points: whether the patient correctly identifies it and knows its indication, dosage, and method of administration. The maximum score is 4, multiplied by the total number of medicines. The assessment of overall adherence is made with the sum of the score obtained for each medication divided by the maximum score [49,50,51]. The scale has not been psychometrically validated in the literature, but it was developed and standardised through expert consensus for institutional use within the regional care programme for polymedicated patients.

##### Primary Caregiver Overload

This will be assessed with the Zarit scale, which consists of 22 questions with answers from 1 to 5 points, with a score ≥ 47 points being considered overburden. High internal consistency was obtained for this questionnaire (Cronbach’s alpha = 0.92) [52].

##### Frailty

The Frail questionnaire, consisting of 5 simple questions on fatigue, endurance, ambulation, comorbidity, and weight loss, will be used. Patients scoring 1 point or more are considered frail. The inter-rater correlation for this instrument was 0.82, indicating good external consistency [53].

##### User Satisfaction

This will be measured through the Satisfad Questionnaire 14, an instrument for evaluation by the patient or main caregiver of the home care services provided, which demonstrated good internal consistency (Cronbach’s alpha = 0.85). Each item is scored on a Likert scale, comprising 4 levels ordered categorically from 0 to 3 (where 0 corresponds to the minimum and 3 to the maximum). The resulting range of possible scores is from 0 to 42 points [54].

### 2.6. Data Collection

Data collection will be carried out by independent evaluators, who will be health professionals from the Salamanca Primary Care Management, with training in the use of the data collection form and the administration of the different tests, which will be paper-based.

The baseline assessment will take place at the patient’s home, and subsequent follow-up assessments will be arranged there or at the health centre depending on their progress:Initial assessment: the variables shown in Table 1 will be collected.Three-, six-, and twelve-month assessment: the same variables as in the initial assessment will be collected, adding the number of readmissions and medicines prescribed, as well as the evaluation of the satisfaction of the user and/or main caregiver.

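### Table 1 schedules no baseline value for therapeutic adherence and section 2.6 does not agree with it, so the comparison between two non-randomised centres cannot be adjusted for where each centre started

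*Protocol article*

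**What the plan says.** **Adherence.** In the data collection block of Table 1 the row "Therapeutic adherence" has ticks at 3, 6 and 12 months and none at the initial assessment. The other outcomes in that block are ticked at all four assessments. Section 2.6 defines the baseline by pointing to the table: "Initial assessment: the variables shown in Table 1 will be collected". For the three follow-up visits it says "the same variables as in the initial assessment will be collected, adding the number of readmissions and medicines prescribed", and then "as well as the evaluation of the satisfaction of the user and/or main caregiver". Adherence is not among these additions. Section 2.5.3 scores each drug on "whether the patient correctly identifies it and knows its indication, dosage, and method of administration" and divides the total by the maximum possible score.

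**Number of drugs.** Section 2.5.3 says "This will be recorded from the electronic prescription of the CPCPs at discharge and at the end of follow-up". Section 2.6 adds it at 3, 6 and 12 months. Table 1 ticks all four assessments.

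**Satisfaction.** Section 2.6 adds it at follow-up only. In Table 1 the row "User satisfaction" is also ticked at the initial assessment.

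**Design and analysis.** Section 2.2 assigns one health centre to the intervention and one to control, and section 2.9 places the study among non-randomised ones. Section 2.8 plans a repeated-measures ANOVA between centres, with covariates such as baseline function, comorbidities or caregiver characteristics.

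**The concern.** In a randomised trial an outcome measured only after the start loses precision but stays unbiased. Here arm and centre are the same thing, and comparability rests on the statement that the two populations are similar. If adherence is first scored at 3 months, an effect that is present by then and sustained shows up only as a constant difference between centres. A difference that was there before the study looks the same.

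The score measures knowledge of one's own medicines. It plausibly depends on cognition and on earlier teaching by the centre's nurses, so a starting difference between centres is credible.

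The conflict between section 2.6 and Table 1 also has a practical side. Evaluators work from a paper form, and a form built from the table would collect different data from one built from the text. A baseline that is not collected cannot be recovered later.

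**Working it through.** **1. The schedules side by side**

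| Variable | Section 2.5.3 | Section 2.6 | Table 1 |
|---|---|---|---|
| Adherence | no timing given | not named as a follow-up addition | 3, 6, 12 months |
| Number of drugs | discharge and end of follow-up | added at 3, 6, 12 months | initial, 3, 6, 12 months |
| Satisfaction | no timing given | added at 3, 6, 12 months | initial, 3, 6, 12 months |

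Section 2.6 allows two readings for adherence. If the baseline set is the column ticked for the initial assessment, adherence is not in it. It is not an addition either, so by the text it is never collected, against three ticks in the table. If the baseline set is every variable in the table except the named additions, adherence is collected at baseline, against the blank cell. Neither reading agrees with Table 1.

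**2. Could another measurement serve as baseline?** The only other adherence assessment is at the one-month visit in section 2.7.2. It is done by the case manager, in the intervention centre only, after case management has begun. It cannot stand in for a baseline.

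**3. The plan's own figure.** Section 2.4 gives a difference of 15 Barthel points, SD 34.8, two-sided alpha 0.05, power 80% and 20% loss.

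- n per group = 2 × (1.960 + 0.842)² × (34.8/15)² = 84.5
- 84.5 / (1 − 0.20) = 105.6, rounded to 106 per group, 212 in total

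The stated 212 reproduces (rounding to 85 before inflating gives 107 per group, 214). It concerns the Barthel Index and does not change here.

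**4. What a missing baseline could do.** The documents give no SD, imbalance or correlation for adherence, so these inputs are assumed and shown as a range. Take 106 × 0.8 = 84.8 completers per group, no true effect, one follow-up visit, equal SDs at both times, and other covariates that remove none of the imbalance. Let d be the baseline difference in SD units and r the correlation of baseline with follow-up.

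- Persisting false difference = r × d
- Standard error = √(2/84.8) = 0.154 SD
- Type I error = 1 − Φ(1.96 − rd/0.154) + Φ(−1.96 − rd/0.154)

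| d | r = 0.3 | r = 0.5 | r = 0.7 |
|---|---|---|---|
| 0.1 | 0.03 SD, 5.4% | 0.05 SD, 6.2% | 0.07 SD, 7.4% |
| 0.2 | 0.06 SD, 6.8% | 0.10 SD, 10.0% | 0.14 SD, 14.9% |
| 0.3 | 0.09 SD, 9.0% | 0.15 SD, 16.4% | 0.21 SD, 27.7% |
| 0.5 | 0.15 SD, 16.4% | 0.25 SD, 37.0% | 0.35 SD, 62.5% |

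**5. Precision.** Without a baseline the detectable difference at 80% power is (1.960 + 0.842) × 0.154 = 0.43 SD. With baseline adherence as covariate it is 0.43 × √(1 − r²): 0.41, 0.37 and 0.31 SD for r = 0.3, 0.5 and 0.7.

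**The case against.** **The blank may be a slip.** Section 2.6 can be read as placing adherence at baseline, so one missing tick might be the whole fault. That is possible, and it is why the point is an inconsistency that leaves no baseline if Table 1 is followed, rather than a proven decision not to measure. The correction is needed either way.

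**Materiality is limited.** Adherence is one of several secondary outcomes and is named neither in the objective nor in the expected results. The article says the scale has not been psychometrically validated, and section 2.9 admits possible residual confounding. All three primary outcomes have baseline ticks. This stands, and it limits the weight of the point without removing it.

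**Stronger readings that the documents do not support:**

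- A reader might infer that the adherence result will be unadjusted. Section 2.8 plans covariates. What is missing is adjustment for baseline adherence.
- A reader might infer that the whole baseline difference becomes bias. Under the model used here only the persisting part, r × d, does.
- A reader might infer that the conflicts over drugs and satisfaction cause the adherence problem. They do not. It comes from the blank cell, and those conflicts are separate.
- A reader might infer that the adherence score lacks its denominator at 3 and 6 months if the drug count is taken only at discharge and at the end. The scale is scored drug by drug, so the number of medicines is known whenever it is given.

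**A tick alone does not secure a pre-intervention value.** Section 2.7.2 starts the case manager's home visit and health education at discharge, Table 1 ticks case management at the initial assessment, and nothing puts the evaluator's visit first. This is right, and the fix takes it up.

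**Conclusion.** The point holds for a secondary outcome. Table 1 and section 2.6 disagree on when adherence is measured. If Table 1 is followed, the comparison of centres cannot separate an effect from the persisting part of a pre-existing difference. That part is 0.03 to 0.35 SD over the assumed range, with a type I error of about 5.4% to 62%. A middle case (0.2 SD, correlation 0.5) gives 0.10 SD and about 10%. These figures illustrate the mechanism and do not forecast this study. They rest on the assumed imbalance and correlation, and on the planned covariates removing none of the imbalance. To the extent that those covariates are related to adherence, the bias would be smaller.

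The contradictory schedules for the number of drugs and for satisfaction are real but separate. For drugs, discharge lies close to the initial assessment, so section 2.5.3 and Table 1 differ in substance at 3 and 6 months. For satisfaction, the difference is the baseline tick.

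**What to change.** 1. In Table 1, tick therapeutic adherence at the initial assessment for both centres, and name it in section 2.6 as a baseline and follow-up variable.
2. State that the evaluator scores it before case management starts where feasible. Where that order cannot be kept, record the dates of both contacts so that it is known which values are truly pre-intervention.
3. Include baseline adherence as a covariate in the follow-up comparison of adherence. Baseline MoCA, already collected, may be added. Follow-up MoCA should not be, because it is itself an outcome that the intervention may change.
4. Separately, give the number of drugs one schedule across sections 2.5.3 and 2.6 and Table 1. Either remove the baseline tick for satisfaction or say in section 2.6 what the baseline value represents.

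The cost is some extra minutes per patient at a home visit that already takes place, more for patients with many medicines, plus changes of wording. No visit is added and the sample size is unchanged. Baseline adjustment removes the imbalance only as far as the scale captures it, so the caution in section 2.9 about unmeasured confounding should stay.
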